#### ***Justification of sample size***

##### Power calculation

The project’s primary outcome measure is the proportion of live-born infants who died in the hospital or health facility in the early neonatal period, i-e, from birth to the day of discharge from facility. Other outcome measures of interest considered are the comparisons of proportions of fresh stillbirths. We computed a sample size for proportion in an unmatched study with 80% power, a one sided alpha of 0.05, and an Inter Class Correlation of 0.0025. The current neonatal mortality rate in Malawi: is 30 per 1000 live births
[19] and assuming a minimum number of clusters of 14 in our sampled districts, the study was powered to detect a 20% difference between the two birth cohorts (intervention and control) in the proportion of live-born neonates delivered by NPCs or staff trained by them) surviving to hospital discharge.

With the allocation of 7 districts per arm with an estimated 700 births per NPC (or staff trained by them), 1028 births per study arm per district would provide sufficient power for a total of 2056 neonates per district. That is, a decline from 30 per 1000 live births to 24 per 1000 live births, rate ratio 0.20.

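### On the protocol's own inputs, the unadjusted comparison in the power calculation has about 32% power for a 20% reduction (ceiling about 40%), not 80%

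*Protocol article*

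**What the plan says.** The Power calculation section of the protocol article describes the method as a sample size for a proportion in an unmatched study, with "80% power, a one sided alpha of 0.05, and an Inter Class Correlation of 0.0025". The control rate is given: "The current neonatal mortality rate in Malawi: is 30 per 1000 live births". The target is a 20% difference ("the study was powered to detect a 20% difference between the two birth cohorts (intervention and control"), spelled out as "a decline from 30 per 1000 live births to 24 per 1000 live births, rate ratio 0.20". The calculation assumes at least 14 clusters, 7 per arm, and concludes that "1028 births per study arm per district would provide sufficient power for a total of 2056 neonates per district".

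Two other sections bear on the point. Study place gives the actual allocation as 8 intervention and 7 control districts. Data analysis plans an interrupted time series by quarter over three years, of which the first 12 months are baseline, comparing intervention with control districts.

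**The concern.** With few clusters, the number of districts limits the information in a cluster trial, however many births each contributes. Seven districts per arm at an ICC of 0.0025 is a tight limit for a difference of 6 per 1000, so a claim of 80% power needs checking.

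At stake is how the result will be read. A published 80% power claim invites readers to take a non-significant result as evidence against a 20% reduction. If the comparison behind that claim has much less power, the inference is not warranted. The question matters here because the trial is meant to inform whether training of non-physician clinicians is sustained.

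**Working it through.** **Inputs, all from the Power calculation section unless noted**
- Control rate p1 = 0.030; intervention rate p2 = 0.024; difference 0.006 (24/30 = 0.80, a 20% relative reduction)
- One-sided alpha 0.05 (z = 1.645); power 80% (z = 0.842)
- ICC = 0.0025
- k = 7 districts per arm (8 v 7 in Study place)
- m = 1028 births per district

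**1. Trying to reproduce 1028.** Births per arm without clustering:

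n = (1.645 + 0.842)² × (0.03 × 0.97 + 0.024 × 0.976) / 0.006² = 6.18 × 0.052524 / 0.000036 ≈ 9,020.

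The plan provides 7 × 1028 = 7,196 per arm, already short. At ICC = 0, z = 0.006 / √(0.052524/7,196) = 2.221 and power = Φ(2.221 − 1.645) = 72%.

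With clustering, the births needed per district are m = n(1 − ICC)/(k − n × ICC). This has a solution only if k exceeds n × ICC = 9,020 × 0.0025 = 22.6. With k = 7 there is none, so 1028 cannot be reproduced for 30 v 24 per 1000.

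**2. Power at the stated figures.**
- Design effect = 1 + (1028 − 1) × 0.0025 = 3.5675
- Effective births per arm = 7,196 / 3.5675 = 2,017
- z = 0.006 / √(0.052524/2,017) = 1.176
- Power = Φ(1.176 − 1.645) = 32%

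**3. Ceiling.** As m grows, the effective size tends to k/ICC = 7/0.0025 = 2,800 per arm. Then z = 1.385 and power = 39.8%.

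**4. Other readings, same formula**

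| Reading | Power for 30 v 24 per 1000 |
|---|---|
| 7 v 7, 1028 births per district | 32% |
| 7 v 7, 2056 births per district | 35% |
| 7 v 7, 4375 births per district | 37.5% |
| 7 v 7, unlimited births | 40% |
| 8 v 7, 1028 births per district | 33% |
| 8 v 7, unlimited births | 41% |
| 14 per arm, 1028 births / unlimited | 51% / 62% |
| 7 v 7, t test on 12 df, 1028 / unlimited | 30% / 37% |
| 7 v 7, two-sided 5%, 1028 / unlimited | 22% / 28% |

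The 4375 figure is an assumption: 50 trainees × 700 births / 8 districts. The document gives no period for the 700 births, and trainees are not spread equally. Fourteen districts per arm is not the design; it is shown only because it is the most generous reading. With a pooled variance, 8 v 7 gives 34% and 42%.

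**5. What 1028 does fit.** For 30 v 18 per 1000 (a 40% reduction), one-sided 5%, ICC 0.0025 and 7 per arm, the required m is 1017 with pooled variance, within about 1% of 1028. Power at m = 1028 is 80.1%.

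**6. Reduction detectable with 80% power, unadjusted**
- 7 v 7: about 40% at 1028 births, 34% with unlimited births
- 8 v 7: about 39% at 1028 births, 34% with unlimited births

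**The case against.** The strongest reply is that the planned analysis is not the comparison in the power calculation. The time series uses a 12-month baseline and randomisation is stratified; both can remove some of the between-district variance that creates the ceiling. This stands. A reader might infer that the trial itself cannot exceed 40% power, or would miss a true 20% reduction about two times in three. The document does not support that stronger reading, because those figures belong to the unadjusted comparison only.

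The gain can be illustrated but not established. Let ρ be the correlation of a district's true rates between years, which the document does not give. Take 7 districts per arm and the assumed 4375 births per district in each period. The correlation between observed district rates is r = ρ × m × ICC / (1 + (m − 1) × ICC) = 0.916ρ. Baseline adjustment multiplies the variance by 1 − r². Power is then about 44% at ρ = 0.5, 53% at 0.7, 62% at 0.8 and 76% at 0.9. At ρ = 0.9 with 8750 births it is about 85%. So 80% is attainable only under favourable assumptions, none of them stated. The power calculation describes an unmatched comparison and takes no credit for the baseline, so its stated justification still fails.

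A second reply is that 1028 is a minimum and the registers will supply all births in each district. That is also fair, but more births lift the unadjusted power only towards 40% (7 v 7) or 41% (8 v 7).

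A third is that an article condenses a fuller protocol. This is not an omission, however: the article prints a complete set of inputs and a result that does not follow from them.

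**Conclusion.** The point holds for the calculation as printed. An unmatched comparison of 30 v 24 per 1000 at one-sided 5%, with ICC 0.0025, 7 districts per arm and 1028 births per district, has about 32% power and cannot exceed about 40%. With 8 v 7 districts the figures are about 33% and 41%. No reading of the stated inputs that was tried reaches 80%, and dropping the clustering altogether does not rescue it (72%).

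That the births figure was computed for a 40% reduction is an inference from the close numerical match; the document does not say so. The figures rest on a normal approximation, equal district sizes and the protocol's own ICC. They say nothing definite about the power of the baseline-using time series, which cannot be calculated from what is given. Nor can it be said in advance that a non-significant result will leave a 20% reduction open, since that depends on the interval observed.

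**What to change.** 1. Reconcile the effect size with the births figure: say which of the 20% reduction and the 1028 births was intended, and correct the other.
2. Restate the power for the allocation actually used. With 8 v 7 districts and ICC 0.0025, an unadjusted comparison has about 33% power for a 20% reduction at 1028 births per district, with a ceiling of about 41%. Equivalently, it detects a reduction of about 34-39% with 80% power.
3. If credit is to be taken for the 12-month baseline, give the power of the planned time-series analysis separately, with its ICC and year-to-year district correlation, either assumed or estimated from the baseline registers.

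This is recalculation and rewording. It needs no extra districts or data; the only cost is a less favourable stated power.

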### Study place

The study will be conducted in districts within the central and northern regions of Malawi. There are a total of 14 districts in these regions which will be randomised to either intervention or control (Dedza, Dowa, Kasungu, Lilongwe, Mchinji, Nkhotakota, Ntcheu, Ntchisi, Salima, Chitipa, Karonga, Mzimba, Nkhata Bay, and Rumphi). A pragmatic decision was made that as Lilongwe is such a large district it would be divided into two with one half randomised to intervention and the other to control making a total of 15 districts. Stratified randomisation of the districts, to ensure the two groups are comparable will be carried out by a statistician at the University of Warwick, UK who will then inform the study team of the outcome. There will be 8 intervention districts and 7 controls. Control districts will be offered the intervention at the end of the trial as part of a randomised waiting-list design.

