### Inclusion criteria

Only NPCs providing emergency obstetric and neonatal care (EmONC) from the 7 randomised intervention districts in central and northern region who have received the intervention training will be invited and those who will give their informed consent will be included in the project or:

The district medical or nursing officers (in intervention districts) or

NPCs, midwives or nursing staff who have been trained by one of the intervention NPCs

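### The target effect is mislabelled (30 to 24 per 1000 is a rate ratio of 0.80, not 0.20), the births are stated in a way whole-district randomisation rules out, and they give about 32 to 34% power, not 80%

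*Protocol article*

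**What the plan says.** All references are to the Protocol article.

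- **Power calculation, effect.** The control rate "is 30 per 1000 live births". The aim is put in words as a 20% difference between the intervention and control birth cohorts, attached to the proportion of live-born infants who survive to discharge. It is then put in figures as "a decline from 30 per 1000 live births to 24 per 1000 live births, rate ratio 0.20".
- **Power calculation, design inputs.** The calculation is done "with 80% power, a one sided alpha of 0.05", and with "an Inter Class Correlation of 0.0025". It assumes at least 14 clusters and continues: "With the allocation of 7 districts per arm with an estimated 700 births per NPC".
- **Power calculation, births.** It asks for 1028 births for each arm in each district, making 2056 infants in each district.
- **Study place.** Districts are randomised whole. The one large district is split, and its halves count as two of the 15, one in each arm. "There will be 8 intervention districts and 7 controls". The Abstract, Study population, Sample size and Procedure sections also give eight intervention districts.
- **Inclusion criteria.** NPCs are to be invited "from the 7 randomised intervention districts in central and northern region".

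**The concern.** The target effect and the number of births are the figures against which a reader judges what the trial could show. Here the effect measure is wrong as printed, the 20% is attached to the wrong quantity, and the births are described as if both arms existed inside one district. Once these are put right, the question is whether the corrected figures deliver the stated 80% power. If they do not, a null result could be read as evidence of no worthwhile effect when the trial had little chance of detecting the effect it names. The count of seven in an eligibility rule is a separate inconsistency with the design.

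**Working it through.** **Inputs (all from the Power calculation unless noted).** p1 = 0.030, p2 = 0.024; one-sided alpha 0.05 (z = 1.645); power 80% (z = 0.842); ICC = 0.0025; m = 1028 births per district; k = 7 districts per arm, or 8 v 7 from Study place.

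**1. Effect label.** 24/30 = 0.80, and 1 − 0.80 = 0.20. The absolute reduction is 6 per 1000. Survival is 1 − 0.030 = 97.0% against 1 − 0.024 = 97.6%, a difference of 0.6 percentage points. A 20% relative rise from 97.0% would exceed 100%, so the 20% can only refer to mortality.

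**2. Births.** Each district belongs to one arm, so a district cannot contribute 1028 births to each arm. Read as 1028 per district and 2056 per intervention-control pair, the total is 14 × 1028 = 7 × 2056 = 14,392, or 7,196 per arm.

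**3. Trying to reproduce 1028.** Births per arm before clustering:

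n = (1.645 + 0.842)² × [0.030 × 0.970 + 0.024 × 0.976] / 0.006² = 6.183 × 0.052524 / 0.000036 ≈ 9,020.

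Over 7 districts this is 9,020/7 ≈ 1,289 per district with no allowance for clustering, already above 1028. A continuity correction gives 1,336, and two-sided tests give 1,636 or 1,684. None of these variants returns 1028.

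**4. Adding the stated ICC.** Design effect = 1 + (m − 1) × ICC; effective births per arm = k × m / design effect. As m grows without limit, this tends to k/ICC:

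- k = 7: 7/0.0025 = 2,800
- k = 8: 8/0.0025 = 3,200

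Both are far below 9,020, so no number of births per district reaches 80% power for 30 v 24.

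**5. Power at 1028 births per district.** Design effect = 1 + 1027 × 0.0025 = 3.5675. Effective births are 7,196/3.5675 ≈ 2,017 for 7 districts and 8,224/3.5675 ≈ 2,305 for 8. Power = Φ(0.006/SE − 1.645).

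- 7 v 7: SE = √(0.052524/2,017) = 0.00510; Φ(1.176 − 1.645) ≈ 32%.
- 8 v 7: SE = √(0.0291/2,017 + 0.023424/2,305) = 0.00496; Φ(1.210 − 1.645) ≈ 33%, or 34% with the pooled variance under the null.
- Unlimited births: about 40% (7 v 7) and 41 to 42% (8 v 7).
- Taking 2056 as births per district at 7 v 7: effective 2,345 per arm, about 35%.

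**6. Effect detectable with 80% power at 1028 per district, 7 v 7.** For 30 v 18 per 1000: n = 6.183 × (0.0291 + 0.018 × 0.982)/0.012² ≈ 2,008, against 2,017 available. The detectable rate ratio is about 18/30 = 0.60.

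**7. District count.** Five sections give eight intervention districts; the Inclusion criteria give seven.

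**The case against.** Much can be said for the protocol, and several stronger readings do not hold.

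- **A reader might infer that the trial was planned for a fall to 6 per 1000.** It was not. The same sentence prints both rates, and the section speaks of a 20% difference. The error is in the label. A true ratio of 0.20 would need only about 62 births per district on these inputs, so 1028 was not built on it either.
- **A reader might infer that 7 per arm in the power calculation is an error.** It can be a planning floor, since the section assumes a minimum of 14 clusters. Moving to 8 v 7 changes power by under 2 percentage points.
- **A reader might see a conflict between 700 births per NPC and 1028.** The first is expected supply and the second is a requirement. Supply above requirement is no contradiction.
- **A reader might think the required total is open between 14,392 and 28,784.** The larger figure takes 2056 births from every district, which rests on the both-arms-in-one-district wording that the design rules out.
- **A reader might infer that the eighth intervention district drops out of the trial.** The Inclusion criteria govern who is invited to interviews and activity records, which Study population ties to the process evaluation. Mortality data come from maternity registers and summaries in all districts.

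The best remaining defence of the power claim is that the analysis uses a year of baseline data, which could raise power above these figures. The article states no baseline correlation and does not credit one in the calculation, so 80% cannot be supported from it. In the other direction, unequal districts and a small-sample correction for 15 clusters would lower power.

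**Conclusion.** The point stands in this form. The rate ratio should read 0.80, the 20% is a reduction in mortality and not a change in survival, and the births per arm within a district cannot describe this design. The larger matter is that correcting the label does not repair the calculation. On the protocol's own rates, ICC, alpha and 1028 births per district, one-sided power is about 32% (7 v 7) to 34% (8 v 7), with a ceiling of about 40 to 42% however many births are counted. This rests on equal cluster sizes, a normal approximation and no baseline adjustment. The births stated correspond to roughly 30 v 18 per 1000. That is an arithmetical match only: nothing in the article shows that this effect was the one used. The seven in the Inclusion criteria is a plain inconsistency that touches the process evaluation and not the mortality comparison.

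**What to change.** In the Power calculation:

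- Give the target as a rate ratio of 0.80 (20% relative, 6 per 1000 absolute reduction) in mortality before discharge, and remove the reference to survival.
- State births per district with each district in one arm, and the total over the districts used.
- Recompute for 8 v 7 districts with ICC 0.0025. Then report either the achieved power for 30 v 24, or the effect detectable with 80% power (for reference, about 30 v 18 per 1000, rate ratio about 0.60, with 1028 births per district at 7 v 7). If baseline data are to be credited, state the assumed correlation.

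In the Inclusion criteria, change seven to eight randomised intervention districts, to agree with the Abstract, Study place, Study population, Sample size and Procedure.

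The cost is wording and a recalculation, and a less favourable stated power. These corrections leave the randomisation and data collection as they are.

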### Inclusion criteria

Only NPCs providing emergency obstetric and neonatal care (EmONC) from the 7 randomised intervention districts in central and northern region who have received the intervention training will be invited and those who will give their informed consent will be included in the project or:

The district medical or nursing officers (in intervention districts) or

NPCs, midwives or nursing staff who have been trained by one of the intervention NPCs

### ***Data collection***

#### ***Quantitative data collection***

Primary data will be extracted from the maternity log (Malawi Ministry of Health Maternity Register, Version 2 (July 2008)) at the district hospital and rural hospitals in each district by the research assistants monitored by the local and UK team. Other facilities within the district (e.g. health Centres) also complete the same maternity log book from which summary data is returned to the district hospital on a monthly basis. These data will also be gathered by the researchers and the combined data will make up a complete picture of the districts. Data will be collected at three points in time. Baseline data will be collected on cases (from the maternity logs and summary logs) for the 12 months prior to the date the training was delivered with two follow-ups at 12 monthly intervals. A paper case report form (CRF) will be produced to facilitate data collection. Data will then be transferred to an MS Excel spread sheet for transfer to the study database.

It is planned that our primary data will be that collected at source (i.e. each district). However, for the purposes of comparisons national data from national databases will also be sourced via our collaboration with the Malawian Ministry of Health for the same time periods.

Within the intervention districts at the three time points (baseline, 12 and 24 months) the research assistants will approach the consenting NPCs (primarily to interview them, described below) but also to gather information about project related activities (e.g. who they have trained, when they did this, how many training session done, etc.).

For process evaluation purposes training registers, adherence to training procedures (during the project period), knowledge scores and training feedback will also be collected and collated from the intervention team. No identifiable data will be recorded

#### ***Qualitative data collection***

In the intervention districts interviews will be carried out at each of the three time points with consenting NPCs (who have received the intervention training). These will be semi-structured interviews about their experiences relating to the project and its impact on practice. District medical and nursing officers in the intervention districts will be invited to be interviewed about the districts involvement in the intervention and at follow-ups how the intervention has worked/fitted in to the hospital routine. As part of the intervention the trained NPCs are expected to cascade the training they have received to others within their districts (e.g. other NPCs or midwives). The research assistants will identify a number of these people from the NPC’s records and they will be approached and interviewed about the training they received and how they have been able or indeed unable to implement what they have been taught. Below is more detail about the interviews. In addition to those already noted we plan to interview the intervention facilitators towards the end of the project again to enhance the process evaluation.

#### ***In-depth interviews with the trained clinical officers***

These interviews will mainly capture what the clinical officers that have been trained think about the training sessions. This will include feelings about the facilitators of the training, the content of the training, the training materials, the training period, and their expectations about the training. In addition participants will also be asked how the training has been beneficial to them, whether it has really improved their skills and also how easy or difficult it has been for them to train to fellow service providers. Plus included in this interview will be:

#### ***Critical incident interviews***

These will be specifically designed to capture the challenges and obstacles that the trained clinical officers met and affected their performance after acquiring the required skills. The interviews will also capture how the trained clinical officers overcame the challenges. This will involve the clinical officers narrating a specific incident or situation e.g. managing a woman with PPH, the obstacle to doing that and how it was overcome. 50 critical incident interviews will be conducted, which means all clinical officers that have been trained in the ETATMBA program will participate.

#### ***In-depth interviews with service providers trained by the trainee clinical officers***

These interviews will focus on how well the trainee clinical officers have implemented the training program to their fellow service providers in their respective districts. Selected service providers that have been trained by the trainee clinical officers will be interviewed on how well they have received the training and on how beneficial they think the training given by trainee clinical officers is to them.

#### ***In-depth interviews with the district medical officer and the nursing officer***

Key personnel in hospitals from which the clinical officers come from will also be interviewed to find out how the Clinical officers have implemented the training program in their respective district hospitals. In addition the key personnel will also give their views on whether they have been changes in the competence and performance of the trained clinical officers after receiving the training as well as on the service providers that have been trained by the clinical officers.

